#### Costs of the lifestyle program

*Health care system viewpoint* – Costs for health care providers and staff (medical visits with corresponding billing, number of hours worked by health professionals and administrative staff), interdisciplinary meetings with case discussion, meetings related to the operation of the program, medical testing, consumables. *Patients’ viewpoint* – Costs for transportation, parking, loss of salary (patient & life partner), daycare.

#### Costs of fertility treatments

*Health care system viewpoint –* Costs for health care providers and staff (idem), drugs, medical testing, consumables, and billing of ART-related investigations or treatments to the public system if applicable. *Patients’ viewpoint* – Costs for transportation, parking, loss of salary, daycare, drugs not covered, and billing of ART-related investigations or treatments to the patient if applicable.

#### Costs of adverse events or complications

*Health care system viewpoint* – Costs of hospitalization or drugs for adverse events related to the lifestyle program, fertility treatments, pregnancy or neonatal care. *Patients’ viewpoint* – Costs for transportation, parking, loss of salary, daycare, drugs not covered, incurred by the patients due to these adverse events or complications.

Data collection will be performed through patients’ charts review, administrative data, questionnaires and interviews with health care providers and staff of fertility clinics for the description of care procedures, as well as questionnaires to patients. At the CHUS fertility clinic, costs will be obtained prospectively and all patients will answer a specific questionnaire; but for the three fertility clinics of comparison, patients’ charts will be retrospectively reviewed. However, as mentioned, a sample of 20 patients will be selected for focus groups: these patients will also answer the same cost questionnaire. Thus, the exact costs from the patients’ viewpoint of the different events will be determined based on these 20 patients and then be extrapolated to the other patients. Departments or directorates of service (billing services at the CHUS, pharmacies, Human Resources, Department of Nursing) will be consulted to match each event to its monetary cost. Where possible, we will use the overhead costs, provided by the administrative services, for a particular treatment and/or complication. When this is not possible, we will conduct interviews with relevant professionals to track the various human resources and materials that were involved.

Since provincial and state pricings for the different outcomes are different, we will only consider a single reference price for each outcome, i.e. pricing in the Quebec health system. In order not to incur double counting in calculating the cost of primary outcome, we will make sure to check the reason for the expense and we will record every cost only once for the primary outcome. Regarding the joint use of equipment or spaces, the cost used will be the unit cost of depreciation for each use or visit. To the extent that the cost measure will be done over a period exceeding one year, we will use a discount rate. The reference discount rate will be 5 % per year. To test the robustness of our results, we also do a sensitivity analysis with rates of 3 and 8 %.

Assessment of quality-adjusted life years (QALYs) and cost-effectiveness of the intervention will be performed using the Short Form-6D (SF-6D). SF-6D is a generic preference-based measure of health derived from the SF-36 Health Survey for use in economic evaluation [54]. It is composed of six dimensions of health: physical functioning, role limitations, social functioning, pain, mental health and vitality. Each dimension has between 4 and 6 levels. The SF-6D defines 18,000 different possible health states, and has a range from 0.3 (worst health state) to 1.0 (best health state) in model 10 [54].

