### Evaluation of clinical outcomes of the lifestyle program for obese infertile women (Objective 2)

The **primary outcome** will be live-birth rates at 18 months. **Secondary outcomes** will be sub-divided into four categories of clinical outcomes:***Lifestyle and anthropometric outcomes***: evolution of anthropometric measures, changes in lifestyle habits (diet, exercise, sleep, alcohol, and tobacco), physical fitness level, daily energy expenditure from physical activities, time spent in various physical activity intensities, step count, evolution of readiness for change, quality of life.***Fertility outcomes***: pregnancy rate (biochemical pregnancy confirmed by a positive beta-human chorionic gonadotropin (β-hCG) level in the serum), spontaneous abortions, multiple pregnancies, spontaneous vs. ART-induced pregnancy, doses of fertility medications, number of treatment or IVF cycles.***Pregnancy adverse outcomes***: gestational diabetes, hypertension, pre-eclampsia, thromboembolism, caesarean section.***Neonatal outcomes***: birth weight, hypoglycemic episodes, Apgar score, jaundice, admission to neonatal intensive care, congenital defects, intrauterine death.

The results obtained at the CHUS will also be compared to those of women with the same criteria who will be seen in three fertility clinics across Canada. At the CHUS, primary and secondary outcomes will be determined using patients’ assessments, questionnaires and review of patients’ records. At the comparative clinics, charts of patients seen during the same time period will be retrospectively reviewed, and administrative data will be gathered.

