### Cost-effectiveness assessment of the lifestyle program for obese infertile women (Objective 3)

Data collected for this objective will trace the operating costs (human and material resources) for each of the patients in the study based on two viewpoints: 1) the costs for the public health system; and 2) the costs for the patients. The two viewpoints will translate into two models of costs for all analyses. The key variable of interest is the total cost per live birth. This variable will be measured in two ways: 1) the total cost per infant alive for all women, which considers costs of unsuccessful interventions; and 2) the total cost per infant alive only for the women who had a live birth. Costs will include:

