Costs of fertility treatments	Review of patient medical record	Throughout the study	Retrospectively
	Questionnaires		
	Administrative data		
Costs of adverse events or complications	Review of patient medical record	Throughout the study	Retrospectively
	Questionnaires		
	Administrative data		
4. Knowledge transfer			
Scientific meeting presentations	ASRM, CSEM, ENDO and other annual meetings	Throughout the study	
Publication in scientific journals	Human reproduction, Fertility and sterility, Journal of clinical endocrinology & metabolism, etc.	Throughout the study	
Presentations to decision-makers and knowledge users	Solicited and unsolicited invitations	Throughout the study	
Diffusion to stakeholders	Conduit, letters, e-mails	Throughout the study	
Executive summary		At the end of the study	

*ART* Assisted reproductive technologies, *β-hCG* Beta-human chorionic gonadotropin, *IVF In Vitro* Fertilization, *ASRM* American society for reproductive medicine, *CSEM* Canadian society of endocrinology and metabolism, *ENDO* Endocrine society, *FertiQoL* Fertility quality of life tool, *OGTT* Oral glucose tolerance test, *WLRT* Weight loss readiness tool

^a^CHUS-RCT: *Centre hospitalier universitaire de Sherbrooke*-randomized controlled trial

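### As listed, the total cost per live birth charges a caesarean but not an uncomplicated vaginal birth, routine antenatal care or a normal newborn stay, so incremental cost is understated

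*Protocol article*

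**What the plan says.** In the Protocol article, the Objective 3 section on cost-effectiveness states: "The key variable of interest is the total cost per live birth". It is to be measured in two ways: "the total cost per infant alive for all women, which considers costs of unsuccessful interventions", and "the total cost per infant alive only for the women who had a live birth". The words "Costs will include" then introduce three headings: the lifestyle program, fertility treatments, and adverse events or complications.

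Pregnancy and newborn care appear only under the third heading. From the health-system viewpoint the entry is "Costs of hospitalization or drugs for adverse events related to the lifestyle program, fertility treatments, pregnancy or neonatal care". From the patient viewpoint, costs count when "incurred by the patients due to these adverse events or complications". Table 2 repeats the same three cost rows, the last being "Costs of adverse events or complications", and has no row for routine maternity care.

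The Objective 2 section places caesarean among the adverse pregnancy outcomes: "hypertension, pre-eclampsia, thromboembolism, caesarean section". The Abstract describes cost per live birth as taking in pregnancy outcomes, and the Background cites the higher cost of pregnancy and delivery in obese women as part of the rationale. The costing text adds that each outcome gets one Quebec reference price and that each expense is recorded once.

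**The concern.** A cost described as total, measured per live birth, should contain the cost of giving birth. Under the three listed headings, a woman with an uncomplicated pregnancy and vaginal delivery adds nothing for maternity care, while a woman delivered by caesarean adds her hospitalisation. No rule says that a complication is costed net of the routine event it replaces. Recording each expense once prevents double counting, but it does not net out a replaced delivery.

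Two results are at stake. The first is the incremental cost of the program, per woman, per extra birth and in any cost per QALY: the arm with more births also has more routine maternity care, and that care is left out. The second is the contrast in delivery costs when caesarean rates differ. The Discussion anticipates a lower cost per live birth and a better cost-effectiveness ratio, so readers will look at exactly these figures.

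**Working it through.** **Inputs.** The Sample size section gives live-birth rates of 25% (control) and 50% (intervention), 58 women per group, 80% power and α = 5%. The protocol gives no unit costs. The routine cost m per birth, the caesarean-to-vaginal price ratio K and the caesarean rates below are therefore assumptions.

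**1. The plan's own figure.** For two proportions, two-sided, with pooled variance and no continuity correction:
n = [1.96·√(2·0.375·0.625) + 0.8416·√(0.25·0.75 + 0.50·0.50)]² / 0.25² = 57.7, so 58 per group. Power at 58 is 80.2%. Then 58 × 1.1 = 63.8, so 64 per arm and 128 in total. The birth rates used here are the ones behind the stated sample size.

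**2. Effect of an omitted routine cost.** Let C be the listed cost per woman in an arm and p its live-birth rate.
- Cost per live birth: C/p as listed, C/p + m when complete.
- Incremental cost per woman rises by m(0.50 − 0.25) = 0.25m.
- Incremental cost per extra live birth rises by 0.25m / 0.25 = m.

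With listed cost set to 1.0 per woman in both arms, and m in the same unit:

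| m | Control, cost per birth | Intervention, cost per birth | Difference | Ratio | Incremental cost per woman | Per extra birth |
|---|---|---|---|---|---|---|
| 0 | 4.0 | 2.0 | −2.0 | 0.50 | 0 | 0 |
| 0.5 | 4.5 | 2.5 | −2.0 | 0.56 | 0.125 | 0.5 |
| 1 | 5.0 | 3.0 | −2.0 | 0.60 | 0.25 | 1.0 |
| 2 | 6.0 | 4.0 | −2.0 | 0.67 | 0.50 | 2.0 |

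The absolute difference in cost per live birth never moves. The ratio and both incremental measures do. The sign can change too: with an intervention listed cost of 0.8, the listed result is a saving of 0.20 per woman. At m = 1 the complete result is (0.8 + 0.50) − (1.0 + 0.25) = +0.05.

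**3. Why 0.25m is an upper limit.** Caesarean stays are already charged, so delivery cost is missing only for vaginal births. At assumed caesarean rates of 40% (control) and 30% (intervention), vaginal births per woman are 0.25 × 0.60 = 0.15 and 0.50 × 0.70 = 0.35. The multiplier for the delivery part is 0.20. With 40% in both arms it is 0.30 − 0.15 = 0.15.

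**4. Caesarean contrast per birth.** Let a vaginal birth cost 1 and a caesarean K. An avoided caesarean is credited with K, but the true saving is K − 1, so the overstatement is K/(K − 1): 3.0 at K = 1.5, 2.0 at K = 2, 1.5 at K = 3. At K = 2 and rates of 40% and 30%, the listed delivery costs per birth are 0.80 and 0.60, a gap of 0.20. With vaginal births priced they are 0.80 + 0.60 = 1.40 and 0.60 + 0.70 = 1.30, a gap of 0.10.

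**The case against.** The strongest reply is that the list is not closed. Its lead-in says what costs will include, not what they are limited to. The Abstract mentions pregnancy outcomes, and the plan for one reference price per outcome could cover a normal delivery. An article may also leave a unit-cost list to a fuller costing document. This has some force: nothing states outright that a normal birth is unpriced. But the third heading itself restricts pregnancy and neonatal costs to adverse events, for both viewpoints, and Table 2 repeats the restriction. The issue is how the stated scope is drawn, not missing detail.

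Three stronger readings are tempting, and the documents do not support them.

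- A reader might infer that the arm with more births looks too cheap on the key variable itself. In absolute terms it does not: a common m adds equally to both arms and cancels.
- A reader might infer two separate errors that both favour the hypothesis. There is one omission, seen on two scales. Per woman, the intervention arm would have more caesareans at the assumed rates (0.50 × 0.30 = 0.15 against 0.25 × 0.40 = 0.10), so charging them adds cost to that arm.
- A reader might infer that the saving from every avoided complication is overstated. For add-ons such as thromboembolism treatment, full cost is the correct increment. The overstatement applies where a complication replaces a routine event.

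It is also fair to say that correction is harder outside the CHUS. The merged hospital database is described only for that site, and the comparison clinics rely on retrospective chart review.

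**Conclusion.** The point holds in a limited form. As listed, the figure is not a total cost per live birth, because maternity and newborn care enter only as adverse events.

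- **Incremental cost:** at 25% against 50% live births, it is understated by up to 0.25m per woman and up to m per extra birth. For the delivery component the multiplier is the difference in vaginal births per woman, 0.20 at the assumed caesarean rates. An understated incremental cost carries into the numerator of any cost per QALY.
- **Relative cost per live birth:** the gap is exaggerated, for example a ratio of 0.50 instead of 0.60 at m = 1 with equal listed costs.
- **Absolute cost per live birth:** a common routine cost has no effect. Bias arises only through replaced events, mainly caesarean (saving overstated 3 to 2 times if it costs 1.5 to 2 times a vaginal birth), or through differing pregnancy losses or multiple pregnancies.

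The actual size cannot be fixed because m, K and the caesarean rates are assumptions. The direction of the incremental error depends on the intervention arm having more births, as the plan expects.

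**What to change.** For the randomised comparison at the CHUS, add a fourth cost category covering antenatal care, delivery and newborn stay for every pregnancy, complicated or not. Price it at the Quebec reference prices already planned, using the obstetric charts and hospital database already in use. Report complications separately as the excess over an uncomplicated course, so that a caesarean counts as an increment over a vaginal birth and add-on treatments keep their full cost. Amend Table 2 to match, and say whether the patient viewpoint covers routine maternity costs.

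For the three comparison clinics, apply the same reference prices to the recorded mode of delivery and outcomes where these are available. Where they are not, state that routine maternity care is excluded and do not call the figure a total cost.

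The cost is some extra unit costing and chart work, since antenatal visits are not hospitalisations, and possibly a few questionnaire items. Cost per live birth will rise in both arms, and with more births in the intervention arm its incremental cost will look less favourable.

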### Ethical considerations

The proposed research was reviewed and approved by the Institutional Research Ethics Review Boards of the CHUS and other fertility clinics. Both research participants and health professionals will be duly informed and consent will be obtained in writing prior to evaluations or focus groups. This includes the 20 patients who will be randomly selected from other Canadian fertility clinics to be evaluated at the end of the study using the same questionnaires and focus group as patients at the CHUS. The main ethical consideration of the proposed research is confidentiality issues that will be minimized. All data will be coded, archived for at least 5 years and then destroyed.

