### Development & implementation of the lifestyle program for obese infertile women (Objective 1)

The Intervention sub-committee will be directly in charge of defining the intervention and planning the implementation. A complete review of the relevant literature will be performed initially and made available to all other committee members. The implementation of the program will be closely monitored by this sub-committee with evaluation of required human, material and other resources; barriers that will be encountered; potential solutions that will be applied; and discussion of difficult cases managed in the program. In addition, a specific qualitative evaluation of the program implementation will take place at the end of the intervention and will be planned by the Evaluation sub-committee. All women included in the CHUS RCT will be evaluated by questionnaires and a sub-group of 20 of these patients will be selected to participate in focus groups. In order to compare health professionals’ and patients’ satisfaction, perceptions and impact of the program on their life to those during usual care in Canada, we recruited three Canadian fertility clinics with different characteristics. In these clinics, 20 patients randomly selected will be evaluated at the end of the study using the same questionnaires and focus group methods. In all four centers, health care providers involved in the fertility clinic and/or the program will also be evaluated by questionnaires and focus groups.

This objective will be under the supervision of our Steering committee and Advisory committee.

Decision-makers from Quebec and Canada who sit on these committees will ensure that our program meets their objectives and is acceptable in terms of required resources and costs. Furthermore, we will validate our program design and evaluation plan with worldwide key experts as well as Canadian obesity experts contacted through the Canadian Obesity Network (CON). We will benefit from the experience of experts involved in the implementation and evaluation of similar programs: the Fertility Fitness program in Australia and the Lausanne Obesity-Fertility clinic in Switzerland.

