#### Patients’ perceptions and satisfaction (Objective 1)

Patient expectations and perceptions of their personal experience regarding weight management, fertility care and pregnancy follow-up, as well as their satisfaction regarding management by their health professionals will be evaluated with questionnaires based on experience from previous studies. A qualitative in-depth analysis of patients’ perceptions of the program and medical care will also enhance our understanding of their personal experience with the program. After the completion of the quantitative evaluation of impact of the program on patients, a theoretical sample based on the technique of critical incidents will be used to create a sub-sample of the whole group. Twenty patients will be recruited in each of the 4 participating clinics (80 patients). To be recruited those patients will have to show certain characteristics (different levels of satisfaction with their care (at CHUS, based on questionnaires), different fertility or pregnancy outcomes, loss or gain of weight during follow-up, etc.). The patients will be participating in a taped-recorded semi-structured qualitative interview to assess their perceptions of impact of their participation into the program (continuity of care, perceptions of changes, contribution to change, quality of life, perspectives of future changes, explanation of level of satisfaction with the program). An interview guide with open-ended questions adapted from the principal variables of the study, the Diabetic Empowerment Scale (DES) [59], and the Impact of Weight on Quality of Life (IWQOL-lite) questionnaire [61] will be used as done in previous studies from members of our group [49, 62].

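### The 20 women per comparison clinic who supply the patient-viewpoint costs are a random sample in two sections and a purposive one in a third, so the extrapolated costs may lack a representative basis

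*Protocol article*

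**What the plan says.** All of these statements are in the protocol article.

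- **Use of the 20.** Under *Costs of adverse events or complications*, every CHUS patient answers a cost questionnaire prospectively, while the comparison clinics rely on retrospective chart review. A focus-group sample of 20, introduced there as already described, also completes the cost questionnaire. The patient-side costs of the various events "will be determined based on these 20 patients and then be extrapolated to the other patients".
- **Random selection.** *Ethical considerations* refers to "the 20 patients who will be randomly selected from other Canadian fertility clinics". *Development & implementation of the lifestyle program* (Objective 1) says: "In these clinics, 20 patients randomly selected will be evaluated at the end of the study", with the same questionnaires and focus-group methods as at the CHUS.
- **Purposive selection.** *Patients' perceptions and satisfaction* (Objective 1) says that "a theoretical sample based on the technique of critical incidents will be used to create a sub-sample of the whole group". It continues: "Twenty patients will be recruited in each of the 4 participating clinics (80 patients" in total). It then sets a condition: "To be recruited those patients will have to show certain characteristics". The traits listed include satisfaction with care, fertility or pregnancy outcome, and weight lost or gained.
- **Planned check.** The limitations in the *Discussion* acknowledge recall bias in these costs and plan the same estimation in Sherbrooke, to be compared with real costs. Selection is not mentioned.

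**The concern.** Costs observed in 20 women can be applied to all other women at a clinic only if the 20 represent the others, or if they are weighted so that they do. A random draw gives that basis. A critical-incident sample is built to show contrast, which suits interviews, but it gives no such basis. The protocol describes what appears to be one group in both ways and then extrapolates from it.

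The patient viewpoint is one of the two cost models, and total cost per live birth is the key economic variable under Objective 3, which includes comparison with the three outside clinics. Whoever draws the sample could follow either rule and still comply with the protocol, and the choice decides which women supply the costs.

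**Working it through.** No figure in the plan can be reproduced here: the protocol gives no unit cost, variance or sample-size basis for the cost sample. The check therefore compares the sections and then asks when selection would matter.

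**Step 1: is it one sample or two?**

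| Section | Selection | Number | Contact |
|---|---|---|---|
| *Ethical considerations* | random | 20 | questionnaires, focus group |
| *Development & implementation* (Objective 1) | random | 20 | questionnaires, focus groups |
| *Patients' perceptions and satisfaction* (Objective 1) | purposive | 20 in each of 4 clinics | semi-structured interview |
| *Costs of adverse events or complications* | not stated | 20 | focus groups, cost questionnaire |

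The purposive rule covers the comparison clinics: 4 × 20 = 80 women, of whom 80 − 20 = 60 are outside the CHUS. Table 2 lists only a questionnaire and focus groups for patients' perceptions and shows no further interview sample. The natural reading is one group of 20 per clinic with two incompatible selection rules. If two groups were meant, the protocol does not say so, nor which one supplies the costs.

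**Step 2: what is extrapolated?** The wording is the cost of each kind of event, and events at the comparison clinics come from chart review. For event type k, let `N_k` be the chart count, `u_k` the true mean patient cost per event at the clinic, and `û_k` the mean among the 20.

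- Estimated total = Σ `N_k` × `û_k`
- Error = Σ `N_k` × (`û_k` − `u_k`)

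The sample's mix of outcomes does not enter through `N_k`. It matters only if it shifts `û_k`.

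**Step 3: when does it shift `û_k`?** For one event type, suppose women with a selection trait have mean cost a per event and the others b. Let p be the share of such events in women with the trait at the clinic, and q that share in the sample.

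- Bias in `û_k` = [q·a + (1 − q)·b] − [p·a + (1 − p)·b] = (q − p)(a − b)

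Under random selection q equals p in expectation, so the bias is zero apart from non-response. Under purposive selection q is set by the recruiter, and the bias is zero only if q happens to equal p or if a = b. Lost salary, travel, daycare and uncovered expenses per event could plausibly differ by satisfaction, outcome or weight change, but the documents do not show that they do. They give none of a, b, p or q, so neither the size nor the direction of any bias can be computed.

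**The case against.** The case for leaving the text alone has four parts.

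1. **The cost section may point to the random sample.** It refers back to focus groups, which is the wording of the random-selection section. The purposive section speaks of interviews and does not mention the cost questionnaire. This is a fair reading, and under it there is no selection bias by design. It is an inference, however: the matching number per clinic and Table 2 suggest a single group.

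2. **Outcome mix does not by itself bias a per-event cost.** This stands. A reader might infer that over-representing women with a live birth must inflate the extrapolated costs. That would follow if a mean cost per woman were carried over, but the protocol describes costs per event, and Step 2 shows no bias from outcome mix alone.

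3. **Sherbrooke provides a check against real costs.** This stands in part. If the Sherbrooke estimate were built from its own 20 women chosen by the same rule, the comparison might reveal some selection effect. But the check is offered for recall bias, does not say which women it uses, and would not separate recall from selection. Nor is it clear that it carries over to two clinics without public coverage of fertility treatments.

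4. **The reach is narrow.** This stands. The comparison is non-randomised, and its retrospective nature is already acknowledged as a limitation.

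Two further inferences are not supported. No passage says that the extrapolated costs will be treated as free of sampling error; how that uncertainty is handled is commonly left to an analysis plan. And the ethics section does not say 20 in all; the perceptions section states 20 in each clinic.

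**Conclusion.** The contradiction is in the current text and needs to be resolved. If the purposive rule governs the cost questionnaire, the per-event costs applied to the other women at the three comparison clinics have no representative basis. They could be biased wherever cost per event varies with satisfaction, outcome or weight change. If the random rule governs, that concern disappears apart from non-response.

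A reader might go further and conclude that the costs will be biased. The documents do not support this: it would require both that the purposive rule applies and that cost per event differs by the selection traits, and neither is established. The size is not computable from what is given.

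Only the patient-viewpoint comparison with the outside clinics is touched. The randomised cost comparison uses questionnaires from all CHUS patients, and the health-system viewpoint and live-birth rate do not depend on these 20 women. The correction is worth making because it is cheap and must be in place before the sample is drawn at the end of the study.

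**What to change.** - State one sampling rule for the cost questionnaire: a random sample of 20 eligible women in each comparison clinic, or a sample stratified by outcome and weighted back to the clinic's own distribution.
- Keep the critical-incident selection for the qualitative interviews only, and say whether the interviewees may overlap with the cost sample.
- State explicitly that the resulting unit costs are applied by event type to chart-counted events.
- Align *Ethical considerations*, *Development & implementation*, *Patients' perceptions and satisfaction* and *Costs of adverse events or complications* with that rule, giving 20 per clinic throughout.

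**Cost.** With separate samples, up to about 20 additional questionnaires per comparison clinic, so at most 3 × 20 = 60. If one stratified, reweighted sample serves both purposes, there are no additional questionnaires, but the interview team gives up some freedom in choosing contrasting cases.
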